## Abstract

**Introduction:** Evidence suggests alcohol consumption is correlated with intimate partner violence (IPV) making alcohol reduction interventions a promising method for reducing IPV. While both financial incentive and cognitive behavioral therapy (CBT) interventions in high-income countries, respectively, have effectively reduced alcohol consumption and IPV perpetration among men, little evidence exists demonstrating that these approaches can work in a low-resource setting.

**Methods:** The objective of this study is to design and pilot test a low-cost, scalable intervention for reducing alcohol consumption and IPV in Bengaluru, India, where alcohol has been shown to be a key driver of high rates of IPV. A pilot randomized controlled trial (RCT) design will be used to examine the feasibility of testing a combined incentive and CBT based intervention among couples to stimulate immediate behavior change and to sustain positive behaviors pertaining to alcohol use and IPV. Sixty couples will be screened and enrolled into one of three study arms: an incentive-only, incentive plus counseling, or a control arm. Extensive procedures have been included to ensure participant safety, including staff training on global safety procedures for violence intervention research, careful messaging of study aims, screening procedures to exclude those at high risk of alcohol withdrawal or severe violence due to the study, and a referral and case management system. Male and female participants will complete surveys at baseline and immediately and 3-months post-intervention. Breathalyzers will be used to capture male participants' blood alcohol content daily for intervention arm participants and three times a week for control participants. A sub-sample of male and female members of couples will participate in qualitative in-depth interviews to further explore pathways to change. The results from this preliminary study will inform the development of a larger RCT study of male alcohol and IPV reduction.

## Introduction

Both experimental and correlational evidence indicate that alcohol consumption can increase the risk of intimate partner violence (IPV). A meta-analytic review of the evidence demonstrates that the association between alcohol consumption and IPV remains significant even when controlling for potential confounding variables, suggesting that at least a portion of IPV risk can be directly attributed to alcohol misuse (1). This link persists when controlling for hostility, antisocial behavior, and norms surrounding aggression (2–4).

Several hypotheses may explain the association between alcohol consumption and IPV; some studies argue that the lowered inhibitions and distorted perceptions of cues resulting from alcohol intoxication may lead to increased aggression (5–7). The Alcohol Myopia Model (AMM), on the other hand, posits that alcohol consumption has a myopic effect on attention, leading intoxicated individuals to focus on the most salient (often provocative) cues in a hostile situation, rather than subtler inhibitory cues (6).

As a result, alcohol reduction interventions are a promising channel for combatting IPV. Several evidence-based individual and couple-level interventions offer potential cost-effective solutions. In particular, there is a large body of evidence supporting the effectiveness of small financial incentives in promoting behavior change in low-resource settings, including India, Mexico, and Tanzania (8–10). In this approach, called contingency management, financial incentives reduce alcohol use by giving drinkers a short-term financial benefit in exchange for abstaining from alcohol use. These financial incentives aim to offset the immediate benefits drinkers might experience from consuming alcohol and make the long-term benefits of avoiding harmful drinking behavior (or conversely the negative consequences of engaging in harmful drinking) salient in the present. Schilbach (10) found that small incentives given to rickshaw drivers in Chennai, India both significantly reduced daytime drinking and increased savings by 60%. In Schilbach's experiment, 229 rickshaw drivers were randomized to one of several conditions involving financial incentives over the course of 3 weeks. Sobriety was measured using a daily breathalyzer test taken at the study office. The study found reduced daytime drinking (i.e., around the time of the breathalyzer tests), however, because drinking at other times increased, overall no reduction in alcohol consumption was observed.

Although small incentives can create short-term behavior change, they do not seem to create long-term change (11). However, when combined with behavioral couples' therapy (BCT) [i.e., couples counseling that uses cognitive behavioral therapy (CBT) as its base] designed to increase sobriety, provide men with alcohol reduction tactics and improve couples' communication (12), an intervention may have more sustained results for reducing IPV and alcohol use. A study in Liberia testing a CBT intervention compared to a CBT and cash-incentive intervention among criminally engaged men found effects were sustained longer among those receiving the combined intervention of cash incentive and CBT (13).

While couples counseling for IPV reduction has historically been controversial, in part due to concerns around safety, a recent call has been made to re-examine this approach, particularly in low-income settings where women have fewer options to leave (14, 15). A systematic review of couples-based therapy for IPV reduction concluded that this approach can be effective, particularly in cases of situational violence and where couples are committed to staying together (16). Of note, several studies included in the review compared BCT with other counseling and intervention approaches among couples where one was using substances. They found that couples receiving BCT reported lower levels of violence at follow-up than participants in other intervention arms (17, 18).

Though the bulk of research on CBT for alcohol and violence reduction has been conducted in high-income countries (19), in part due to a lack of high-skilled counselors in low-resource settings and the cost of training such counselors, one study in India suggests that this counseling can be feasibly conducted by trained lay counselors (20). A second study in India suggests this approach may be effective in reducing IPV perpetration among men with harmful drinking (21). In this latter study, of 177 alcohol dependent men who screened positive for IPV perpetration in Bengaluru, those who were randomized to receive CBT had significantly lower levels of IPV perpetration 3 months following the intervention.

Together, these bodies of work suggest a promising avenue for reducing IPV in resource-constrained settings. Thus, in this pilot study using a randomized controlled design we intend to examine the feasibility of testing a combined incentive and BCT based intervention to stimulate immediate behavior change and to sustain positive behaviors pertaining to alcohol use and IPV, which will inform the development of a larger RCT study (22).

## Materials and methods

### Objectives

Given the lack of existing rigorous research on reducing alcohol use and IPV in developing countries, we aim to begin filling the gap by conducting our work in an urban slum settlement in Bengaluru, India. Feasibility of the study will be evaluated through the following specific objectives:
Ability to recruit, enroll and retain couples in the two intervention arms and the control arm;Ability of male participants to consistently use breathalyzers as a measure of sobriety; andCouple's level of engagement with BCT sessions.

We will also assess preliminary effects of the intervention on primary outcomes including household safety and male partner sobriety, as well as on intermediate outcomes including attitudes and behaviors related to gender equality and shared household decision-making, which are relevant to longer-term outcomes of IPV prevention.

### Study design

This study is a randomized control pilot study of *Beautiful Home*, an innovative combined incentive-based and BCT intervention developed with input from community partners for the mitigation of male alcohol use and IPV among couples in a slum in Bengaluru, India. Figure 1 depicts our Theory of Change (TOC). We hypothesize that the *Beautiful Home* intervention is feasible and can be delivered safely, leading to improvements in short-term alcohol reduction as a result of financial incentives. When combined with BCT, we posit the intervention will enable couples to learn skills that will support longer-term change related to alcohol use and IPV. Based on the results of this pilot, we will refine our approach, and determine the merit of a future phase 3 trial of the intervention.

**Figure 1 F1:**
[figure not shown]
*Beautiful Home* intervention Theory of Change (TOC).

The study will be conducted with 60 couples randomized into one of three arms: an incentive-only arm, an incentive-plus-counseling arm, and a comparison arm. The design mimics the proposed design of a follow-on randomized control trial, and allows for testing the feasibility and acceptability of the study design, as well as offering an opportunity to determine whether the combined approach of incentives and counseling performs better than an incentive-only intervention. During the intervention, breathalyzer data will be collected daily for the first 4 weeks from men using Soberlink© breathalyzer technology that allows for photo capture to ensure the appropriate person is taking the test. A period of 4 weeks was chosen for the incentives portion of the intervention based on the duration of Schilbach's study (10) and to preserve the team's flexibility to adapt if the initial incentive structure was not affecting drinking. Participants in the incentive-plus-counseling arm will participate for an additional 2 weeks (6 weeks) to accommodate counseling sessions. No breathalyzer data will be collected for the additional 2 weeks. Women and men will complete a baseline survey, as well as surveys immediately and 3 months post-intervention. A sub-sample of male and female participants from each study arm (~4 couples per arm) will participate in qualitative in-depth interviews to gain feedback about their participation in the intervention, including around processes of change (i.e., what pathways contribute to changes in alcohol and violence reduction) that might inform the content of future interventions. See Figure 2 for a diagram of study flow and data collection points.

**Figure 2 F2:**
[figure not shown]
Flow diagram of the progress through the phases of the 3-arm randomized trial of enrollment, allocation to intervention arm, and data collection points.

### Study setting

The study will be conducted in Jaya Nagar slum in Bengaluru, India, where the research team has a history of engaging with a local community-based organization, Association for Promoting Social Action (APSA), through their self-help groups (SHGs). The chosen slum was selected in collaboration with this partner based on combined prior experience in the community and characteristics relevant to the proposed objectives of the pilot study that could ultimately contribute to the scalability of the intervention. These characteristics include low socio-economic status of residents, high levels of current alcohol use and IPV, social norms that demonstrate perceived acceptability of alcohol use and IPV, and inequitable gender norms.

### Randomization

Participants will be randomized at the couple-level prior to the start of the intervention by a statistician using a random number generator. Their randomization assignment will be revealed during an orientation session using a sealed envelope with their study ID.

### Study population

Our screening procedures will be designed to identify couples who would benefit from the study (i.e., those with problems related to alcohol and IPV), as well as to minimize the potential risk experienced by participants. The protocol achieves this by screening out men with severe alcohol dependence and experience of severe violence among women. The screening tool for men will utilize the AUDIT-C (23) to screen out non-drinkers and the Severity of Alcohol Dependence Questionnaire (SADQ) to screen out men with severe alcohol dependence syndrome. The SADQ was chosen based on its prior use by the World Health Organization (WHO) in multiple low-income countries, and its reliability and validity (24). During the screening process, men who score 31 or higher on SADQ and are deemed to be severely dependent will not be included in the study. Men who score as moderately dependent (16-30 on the scale) will be initially waitlisted until the team can determine the safety of enrolling these participants considering the possibility that these individuals may develop severe or complicated alcohol withdrawal syndrome requiring medical intervention. This subset of men will undergo a second medical screening by the study physician using the Clinical Institute Withdrawal Assessment for Alcohol Scale (CIWA-AR) (25) and those scoring above 8 on this scale will be excluded from the study.

While Standard WHO questions (26) on violence have been reliably used to measure violence in low and middle-income countries, no studies were identified that clearly documented procedures for screening out women experiencing severe violence whose risk may be increased by a couples-level violence prevention intervention. Following a risk averse model, the study team initially defined severe violence as the following types of violence occurring in the past two years: (a) being hit with a fist or something else that could hurt you on purpose, (b) being kicked, dragged, or beaten up on purpose, (c) being choked or burnt on purpose, and (d) being threatened or abused with a gun, knife, or other weapon. However, upon further discussion with stakeholders, our community-based partner, and pre-testing of the screening tool, we realized that these criteria would exclude most women experiencing violence and thus limit our ability to reach women in need of the intervention. As such, our screen-out criteria were adjusted to exclude women being kicked, dragged, or beaten up on purpose six or more times in the past 6 months, or those who were choked, burnt on purpose, threatened or abused with a gun, knife, or other weapon at any time in the past 6 months. Ever being hurt badly enough to require medical attention remained an exclusion criterion. All women who are screened out will receive access to referral resources for violence. In summary, the participant eligibility criteria include the following: (1) female partner between 18 and 40, (2) married, (3) speaks Kannada, (4) female partner reports male partner has a drinking problem, (5) female partner ever experienced psychological violence, and or physical, or sexual violence perpetrated by their male partner less than six times in the previous 6 months, and (6) both partners willing and able to enroll. Couples will be excluded if (1) the male partner is deemed to be severely alcohol dependent or at risk of severe alcohol withdrawal symptoms; (2) the female partner reported occurrences of severe physical or sexual violence characterized by attempting to choking or burning and threaten to use or actually used a knife or other sharp weapons against her or ever hurt badly enough that required medical attention; or (3) one or both members of the couple feared the counseling sessions may increase violence. Additional details regarding eligibility determination are described later.

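### The severe-violence screen is stated twice under Study population, and the two current versions count different acts toward six in 6 months

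*Protocol article*

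**What the plan says.** All the relevant text is in the Protocol article, Study population. An initial definition of severe violence with a two-year look-back is described and then replaced, so it is not part of the conflict. Two current statements follow.

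- **Adjusted screen-out rule.** The criteria were changed to "exclude women being kicked, dragged, or beaten up on purpose six or more times in the past 6 months", and also to exclude women who were choked, burnt, or "threatened or abused with a gun, knife, or other weapon at any time in the past 6 months". In addition, "Ever being hurt badly enough to require medical attention remained an exclusion criterion".
- **Summary list.** It opens with "In summary, the participant eligibility criteria include the following". Inclusion item 5 asks that the woman has ever experienced psychological violence, then continues with *and or* and "physical, or sexual violence perpetrated by their male partner less than six times in the previous 6 months". Exclusion item 2 covers severe physical or sexual violence, described as "attempting to choking or burning and threaten to use or actually used a knife or other sharp weapons against her", or a lifetime injury that needed medical care.

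The section closes with "Additional details regarding eligibility determination are described later".

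**The concern.** A summary should restate the rule it summarises. This one counts a wider set of acts toward the threshold and drops the time window on the gravest acts. Both statements are written as current, so the difference cannot be put down to superseded text.

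The rule matters because the section gives "screening out men with severe alcohol dependence and experience of severe violence among women" as the way the protocol keeps risk to participants down. Under Recruitment and enrollment, a couple is enrolled once both partners are found eligible. The rule therefore decides which women are judged too much at risk for a couples-level intervention, and which are turned away from a 60-couple pilot meant to inform a larger trial.

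**Working it through.** No sample size, power or error rate is involved, so the check is a comparison of the two texts followed by test cases.

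| Element | Adjusted rule | Summary list |
|---|---|---|
| Acts counted toward six in 6 months | Kicking, dragging, beating | Physical or sexual violence generally (inclusion 5) |
| Limit on sexual violence | None stated | Fewer than six in 6 months (inclusion 5) |
| Window for choking, burning, weapon acts | Past 6 months | None stated (exclusion 2) |
| Link between choking/burning and weapon acts | *or* | *and* |
| Weapons | Gun, knife, any other | Knife, other sharp weapons |
| Injury needing medical care | Ever | Ever |

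The last row agrees; the others do not. In the cases below, each woman has no trigger other than the one named and has never had an injury needing care. The *and* in exclusion 2 is read as *or*, and its weapon list as any weapon.

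1. **Slapped or sexually coerced six times in 6 months, never kicked, dragged or beaten.** The adjusted rule does not exclude her. Under the summary she fails inclusion 5 if the limit binds. Three slaps plus three sexual acts (3 + 3 = 6) give the same split.
2. **Choked 12 months ago.** The adjusted rule does not exclude her, because 12 months is outside the 6-month window. Exclusion 2, read literally, does.
3. **Choked more than two years ago.** The adjusted rule does not exclude her, and nor did the superseded two-year definition. Exclusion 2, read literally, does. On these acts the summary is thus stricter than the definition the authors gave up because it would shut out most women experiencing violence.
4. **Beaten up six times in 6 months, with psychological violence also present.** The adjusted rule excludes her. The summary alone also excludes her if the limit binds. If *and or* means that psychological violence is enough for inclusion 5, the summary alone admits her. If both texts are applied, she is excluded on either reading.

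The later sections were then checked for the promised detail. Recruitment and enrollment, Intake process and Study activities by arm describe process only. The Discussion says that the threshold was adjusted but does not restate it.

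**The case against.** The best defence is that inclusion and exclusion criteria are applied together: a woman must satisfy inclusion 5 and must not trigger the screen-out rule. On that view there is one rule set with a poorly condensed summary, and nobody beaten six or more times is enrolled. The second half of this stands. The first half does not remove the problem, because applying both texts literally refuses the women in cases 1 (if the limit binds), 2 and 3, whom the adjusted rule does not exclude.

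A second defence is that exclusion 2 merely omits a window stated shortly before, so the reader should carry it forward. That is plausible, and the look-back point is therefore secondary. Condensation cannot explain inclusion 5, because a summary that shortens does not turn three named physical acts into all physical or sexual violence.

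Three stronger readings are tempting, and the document does not support them.

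- A reader might infer that the protocol lets severely beaten women in. That needs both the summary used in place of the adjusted rule and the looser reading of inclusion 5. Other safeguards also remain: the lifetime injury criterion, exclusion where either partner fears that counseling may increase violence, and the check-in calls, case management and shelter described under Safety procedures and ethical approval.
- A reader might infer bias between arms. Eligibility is settled before couples learn their arm, and nothing in the text links the discrepancy to allocation.
- A reader might infer that staff applied different rules to different women. The eligibility questionnaire is not shown, so this cannot be said.

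**Conclusion.** The point holds as an inconsistency in a safety criterion as written. The firm part is the set of acts counted toward six in 6 months, together with the unclear *and or* in inclusion 5. The missing window, the *and*, and the narrowed weapon list in exclusion 2 are secondary.

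The likely direction is over-exclusion of women whom the relaxation was meant to reach. Given the assumed reading of exclusion 2, the less protective result is confined to the one combination in case 4. Taken to the letter and used alone, exclusion 2 would also miss a threat with a gun only. That is treated here as a wording slip to correct, not as evidence of an intended looser rule.

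The share of women affected cannot be computed, because the document gives no distribution of violence types or timing. No analysis, sample size or error rate changes. It should be fixed, because the rule governs participant safety and the correction is cheap.

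**What to change.** Make the summary match the adjusted rule. Exclude a woman, whether or not psychological violence is present, if any of these applies:

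- she was deliberately kicked, dragged or beaten up on six or more occasions within the past 6 months;
- within the past 6 months she was choked or burnt, or was threatened or abused with a gun, knife or any other weapon, even once;
- she was ever hurt badly enough to need medical care.

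Reword inclusion 5 so that it states only the violence required for entry: psychological, physical or sexual. If the safety team also wants a limit of six in 6 months on sexual or other physical violence, write it as an explicit exclusion in both places. Then check that the eligibility questionnaire under Recruitment and enrollment uses the same rule.

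The cost is a wording change, a check of the questionnaire and possibly a notification to the ethics committee. An added limit on sexual or other physical violence could slow recruitment, by an amount the document does not allow one to estimate.

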### Safety procedures and ethical approval

Studies have shown that interventions targeting women experiencing IPV can result in an escalation of violence and the participants' safety being compromised (27). Based on our past experience in recruitment of women experiencing IPV, a multi-step recruitment process has been developed, with eligibility confirmation, provision of detailed information regarding the study and informed consent occurring at a designated community center, which provides a confidential and safe space. We initially designed to contact and consent female partners first in order to offer them the opportunity to weigh the risks and benefits of participation before providing consent and allowing the research team to contact their male partner. A similar approach was successfully implemented in a study recruiting mother-in-law's of young pregnant women experiencing abuse in Bengaluru (28).

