#### Comparison arm

Activities for the comparison arm will consist of prompts to men via cell phone messages to breathe into their breathalyzer once every other evening. Breathalyzer scores and a photo of the participant's face will be immediately recorded and stored in the Soberlink© system. The participation reward will be split into immediate earnings (which participants can come into the office to collect throughout the study) and savings (which will be deposited into their bank accounts as a lump sum at the end of the study). At the conclusion of the intervention period, men enrolled in the comparison arm will participate in a 60–90 min, community-requested alcohol education module focusing on couple's conflict management and economic goals.

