#### Incentives arm

Couples enrolled in the incentives arm will participate in all of the activities described above for the comparison arm except that they will receive twice-daily prompts to breathe into their breathalyzer. Given our intention to combat IPV, which generally was posited to occur in the evenings when both partners are home, this pilot study incentivized sobriety in the evenings by scheduling daily breathalyzer tests in the evenings and early mornings. Couples will learn how the incentives are tied to breathalyzer scores and will be walked through a goal-setting exercise in which couples decide on goals they would like to save for such as children's education savings goals, individual savings goals, and business savings goals. Like comparison arm participants, daily and weekly activities for the incentives arm also consist of daily prompts to men to breathe into their breathalyzer via cell phone messages; however, these men will receive larger incentives for negative breathalyzer tests. Men will come in to the study office to receive their participation fees and a proportion of their breathalyzer test rewards, and will allocate another portion of the incentives to the goals they selected during the orientation session. A distinction was made between immediate rewards and long-term rewards for saving in our study design to allow men to feel that they were earning money for their behavior change that they could control, while also addressing a need to ensure the intervention contributed positively to family goals and shared financial decision-making with their female partners.

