#### Incentives and counseling arm

Finally, those couples in the incentive and counseling arm will participate in all activities described for the incentives arm and also decide on a day of the week and time to come for BCT counseling. There will be a total of four sessions covering topics related to alcohol use, relationships, and communication. Each session will last for approximately 1 h. Sessions will be conducted by lay counselors who will be trained on BCT facilitation. Additionally, a clinical psychologist trained in CBT (ST) will supervise counselors and observe a subset of counseling sessions to monitor fidelity and measure quality of implementation.

While BCT is generally conducted over a significant duration of time rather than constrained to a discrete number of sessions, our pilot was designed to test the feasibility and resonance of key concepts and activities. The first BCT session will include an introduction to a “daily trust contract” during which the male partner verbally commits to reduce his drinking and his female partner acknowledges her support. The first session will also include a relaxation exercise to aid in overcoming the urge to drink. During the second session, the daily trust contract will be revisited and an activity to identify and avoid triggers to alcohol use on the way home will be introduced. Other strategies to avoid drinking will also be discussed, including the relaxation exercise, reviewing positive reasons for sobriety, distracting activities, and positive self-talk. The third session will include a review of prior alcohol avoidance strategies, as well as an activity aimed at encouraging caring behaviors between partners. In the final session, couples will review the caring behavior activity and will be introduced to the concept of active listening. All sessions will include role plays and end with assignments that couples will be asked to practice between sessions.

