### Sample size

The sample size is anticipated to be 60 couples (20 per intervention arm). While this sample size is not powered to detect significance, it is similar to that used in our prior research of pilot interventions and is in line with recommendations that studies of this kind have a sample size of 24–50 (33–35). We anticipate attrition of approximately 20%, so our goal is to enroll 10–12 more couples to buffer these losses, yielding a final sample size of around 60 couples.

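### The fear-of-violence exclusion covers only the counseling sessions, so it is narrower than the stated screening aim and than what couples in the three arms will receive

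*Protocol article*

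**What the plan says.** The Abstract lists among the safety procedures "screening procedures to exclude those at high risk of alcohol withdrawal or severe violence due to the study". The Study population section then sets out three exclusions. The first concerns severe alcohol dependence or withdrawal risk in the man. The second concerns severe violence that the woman has already experienced. The third applies where "one or both members of the couple feared the counseling sessions may increase violence".

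Under Study design the couples are randomized to "an incentive-only arm, an incentive-plus-counseling arm, and a comparison arm". The components of each arm are:

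- **Comparison arm:** "prompts to men via cell phone messages to breathe into their breathalyzer once every other evening", a participation reward, and an education module for the men at the end.
- **Incentives arm:** the same activities with more frequent testing, a goal-setting exercise for the couple, and payment tied to results: "these men will receive larger incentives for negative breathalyzer tests".
- **Incentives and counseling arm:** "those couples in the incentive and counseling arm will participate in all activities described for the incentives arm and also decide on a day" for the counseling sessions.

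On the general risk, the section on safety procedures says that "interventions targeting women experiencing IPV can result in an escalation of violence and the participants' safety being compromised".

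**The concern.** The third exclusion differs in kind from the other two. They rest on the man's dependence or withdrawal risk and on past acts of violence. The third uses each partner's own forecast of harm from participating. The forecast is asked about one component only, and most couples will not receive that component. The components that most or all couples will receive are not named.

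The omitted components are not obviously neutral. The Incentives arm section ties money to breath-test results and directs part of the earnings to goals the couple has chosen. It places tests in the evenings and early mornings because partner violence was thought to occur mainly in the evening, when both partners are at home. A partner could reasonably worry about the reaction to a failed test or lost earnings and have no worry about counseling.

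Two features of the protocol give the forward-looking question more weight. The past-violence threshold was relaxed because the initial definition would have removed most women experiencing violence. The plan to approach women first was also changed to allow men to be recruited first. At stake is whether the stated entry criteria match the risk they are meant to control, in a pilot whose procedures are meant to be carried into a larger trial.

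**Working it through.** No power or error-rate figure is involved. The check compares the criterion with the stated aim, the timing of allocation and the content of the arms.

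**1. Which criteria look forward?** Inclusion (5) and exclusion (2) concern violence already experienced. Exclusion (1) concerns dependence and withdrawal. Inclusion (6) requires both partners to be willing and able to enroll, but does not ask about expected violence. Only exclusion (3) does, and its object is the counseling sessions. The Study population section refers to further eligibility detail later. The later sections on recruitment, intake and study activities describe process and add no wider fear criterion.

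**2. Is the arm known when the criterion is applied?** No. Under Recruitment and enrollment, couples enroll once both members are deemed eligible. Under Study activities by arm, they come to orientation after that. Under Randomization, the assignment is revealed at orientation from a sealed envelope. The criterion therefore applies to every couple, any of whom may be allocated to any arm.

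**3. How many couples receive each component?** The Sample size section states: "The sample size is anticipated to be 60 couples (20 per intervention arm"). With three arms and 60 couples, this means 20 in each arm, the comparison arm included.

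| Component | Arms | Couples | Share | Named in exclusion (3) |
|---|---|---|---|---|
| Counseling | 1 of 3 | 20 | 20/60 = 33% | Yes |
| Incentives for sobriety | 2 of 3 | 20 + 20 = 40 | 40/60 = 67% | No |
| Breath testing | 3 of 3 | 20 + 20 + 20 = 60 | 60/60 = 100% | No |

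For 60 − 20 = 40 couples, the only forward-looking violence criterion refers to something they will not receive. Of these 40, 20 have incentives and breath testing, and 20 have breath testing with a participation reward. The shares depend only on equal allocation, so they would not change if extra couples were enrolled to offset attrition.

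**4. Does the scope match the aim?** The Abstract speaks of severe violence due to the study. The Study population section speaks of women whose risk a couples-level intervention may raise, and the safety section speaks of interventions in general. None of these is limited to counseling. Exclusion (3) is.

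**The case against.** The strongest reply is that exclusion (3) is an added layer, not the main safeguard. The Study population section presents the dependence and past-violence criteria as the means of limiting risk, and they apply whatever the arm. On that reading the Abstract and the criteria do not contradict each other. This stands in part: the past-violence criteria do serve the Abstract's aim, so it would be wrong to say that exclusion (3) alone serves it. They do not record what a partner expects, however, and where the plan does ask that, it asks too narrowly.

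A second reply is that a fearful woman can decline. Her written consent is required, both partners must be willing, and intake takes place in a confidential setting with a private alternative. This also stands. A reader might infer that such a woman would be enrolled, but the documents support only that exclusion (3) does not exclude her. Recruiting the man first may weaken refusal as a safeguard, although the protocol reports that women often wanted that order.

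Third, a reader might infer that the screen never asked about incentives. That cannot be known. The screening tool is not shown, and the criteria are given as a summary in a journal article. What can be said is that the criterion is stated, its scope is explicit, and that scope is narrow.

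Fourth, a reader might infer that the safety conclusion for the incentives arm rests on this screen. It does not. Under Expected outcomes and results it depends on whether harmful events directly related to the intervention are detected. The check-in calls, case management, community liaisons and shelter are not described as limited to the counseling arm. They act after enrollment, so they do not alter the entry criterion. Nor do the documents say that breath tests are taken at home.

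Finally, there is a visible reason for naming counseling: the Introduction notes that couples counseling for partner violence has been controversial on safety grounds. That explains the wording. It does not explain leaving out the other components.

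**Conclusion.** The point holds as a mismatch of scope. The only listed criterion on expected violence names a component planned for 20 of 60 couples. It leaves out one planned for 40 and one planned for all 60, although it is applied before any couple's arm is known. It is therefore narrower than the aim stated in the Abstract.

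The figures of 33%, 67% and 100% count planned exposure under equal allocation. They do not estimate how many partners fear the incentives or the testing, do not fear counseling, and would still consent. The documents give no figure for that group, and it may be very small. The conclusion rests on the criterion as worded in the article; if the screening tool already asks about the whole study, only the published wording needs correcting. No statistical quantity in the plan changes.

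**What to change.** Reconcile exclusion (3) with the aim stated in the Abstract and with the three-arm design. The fear-of-violence criterion should cover taking part in any arm to which the couple may be allocated: breath testing, incentives and savings goals, or counseling. Each partner should be asked separately and in private, within the existing eligibility questionnaire and before allocation. If the screening tool already does this, bring the criterion in the protocol into line with it.

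The cost is one reworded criterion and one reworded question. The downside is that some additional couples may be screened out, and the documents give no basis for a number. This matters for a 60-couple pilot in which the ability to recruit is itself an objective, and the protocol records that its initial, broader violence criteria would have excluded most of the women it hoped to reach. Recording which component a partner fears, for each couple screened out on this criterion, would show how much of any recruitment loss comes from the wider wording.
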